#### Statistical analysis

All analyses will be performed on a full intention-to-treat basis, (all patients randomized will be included) and all patients will be analyzed according to their allocated group, whichever treatment they received. We will calculate the percentage of registered patients who were randomized, with 95% confidence interval. We will also calculate the percentage of patients experiencing recurrent VTE recurrence and bleeding events in both groups with 95% confidence intervals. The percentage of patients who died within six months of randomization will be calculated in both arms, along with the percentage of patients who successfully completed six months of trial treatment in the LMWH group. The median QLQ-C30 raw and linear transformed functional scales will be calculated and presented for both arms of the study. No formal subgroup analyses are planned. However, if any treatment effect is found we will investigate whether it is consistent across participant subgroups (defined by all pre-treatment factors collected) although this analysis will be exploratory in nature. Exploratory analyses may be conducted to aid hypothesis generation if a phase three RCT is subsequently developed.

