Currently, clinical guidelines recommend clinicians consider continuing anticoagulation indefinitely in patients with locally advanced or metastatic cancer [15,16,22]. Such recommendations are based largely on consensus opinion and, to date, have been supported by limited clinical evidence beyond case series and observational studies [23,24]. In the recently reported DALTECAN (Dalteparin sodium for the long-term management of venous thromboembolism in cancer patients) study, 334 patients with VTE and locally advanced or metastatic cancer were treated with dalteparin, of whom 185 (55.4%) completed six months of therapy and 109 (33%) completed twelve months [24]. The authors reported a 10.2% overall frequency of major bleeding and an overall incidence of new or recurrent VTE of 11.1%. In patients treated during the extended anticoagulation period, new or recurrent VTE was reported in 4.1% of patients and major bleeding at a rate of 4.2%. It is notable that both bleeding and recurrent thrombosis rates were higher in the first six months of anticoagulation (1.3% and 1.4% per patient-month respectively) compared with months seven to twelve (0.7% and 0.7% per patient-month respectively) [24]. In the absence of a control arm in which patients received placebo/ceased anticoagulation at six months, the study offers no further guidance as to whether anticoagulation beyond six months provides any net benefit. However, it offers valuable data, which can be used to inform future clinical studies. Firstly, with 96% trial adherence, it suggests that the use of LMWH beyond six months is feasible within the trial setting. Secondly, it suggests that safety concerns regarding bleeding in this patient group may be less of an issue than previously believed. Furthermore, with the rate of VTE recurrence being lower during the extended anticoagulation period than the initial six months, it would seem reasonable to question what degree of added clinical benefit is gained through extended treatment, rather than ceasing anticoagulation at six months [24]. Finally, the trial did not formally evaluate quality of life aspects of LMWH administration over an extended time period.

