#### RCT sample size calculation

We anticipate there being at least 200 eligible patients per year in total from all three recruitment settings. We assume that not all patients who have been injecting LMWH for five months will agree to continue for a further six months. We are not sure what proportion of patients will be willing to be randomized, but we consider that at least 30% will need to agree in order to make a phase three RCT worthwhile. Therefore, the ALICAT study will aim to assess the feasibility of randomization by determining if at least 30% of potential patients will agree to randomization. We will then calculate the precision of this proportion with a 95% confidence interval. We will also estimate the proportion of patients who experience recurrent VTEs during follow up, which will inform the design of the phase three RCT.

If less than 15% of eligible patients agree to take part in the trial, a phase two RCT may not be suitable as we may not be able to recruit suitable numbers, given that a larger phase three RCT could have more stringent eligibility criteria as a result of this feasibility study. If at least 30% agree to take part, then we would consider that randomizing patients to a larger phase three trial would be feasible. Using a Fleming’s single stage design, setting p1 to 0.15 and p2 to 0.3, and with 5% significance and 90% power, then we will need to approach 62 eligible participants with details of the trial. This design requires that at least 15 out of 62 participants consent to the trial. We therefore propose a two-stage sample size. If at least 15 out of the first 62 participants recruited to the trial accept randomization, then we will continue recruitment into stage two. If fewer than 15 patients agree, we will determine at this stage that randomization within this population is not feasible.

If we expect that 200 will be the maximum potential number of eligible patients, then we can expect to be able to produce a 95% confidence interval for the percentage willing to be randomized of width 13.7% or less. For example, if the percentage is 50%, then we could expect the 95% confidence interval to be 43.15 to 56.85%. If the percentage is 30% we can expect a slightly smaller confidence interval of 23.7 to 36.3%. If only 150 patients are deemed eligible, then we can expect to calculate a 95% confidence interval for 50% randomized of 42.1 to 57.9%.

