Our target registration number for this feasibility trial is therefore 200 patients, of which we hope that at least 60 patients will be randomized into the two groups. Thirty patients per arm will provide enough power to create a 95% confidence interval around the risk of VTE recurrence, which would have a width of 34% or less. As an example, if we found that the risk of VTE occurrence was 50% in the arm that stopped, we would be able to estimate a confidence interval of approximately 33% to 67% or smaller. If the risk of VTE were 8%, the confidence interval would be 0 to 19%.

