#### RCT data collection

Participants randomized to the RCT will be seen at the recruiting hospital clinical or GP practice (as appropriate) approximately 12 and 26 weeks after starting a further six months treatment with LMWH (treatment arm) or after stopping treatment with LMWH after six months treatment off-trial (control arm). Assessments will include VTE treatment and compliance, physical assessment, full blood count, urea, electrolytes, liver function test, bone profile, toxicities, concomitant medications, use of NHS resources (hospital admissions, GP visits, nurse visits: details to be taken from patient diary booklet and patient notes), and quality of life questionnaires (EORTC QLQ-C30, E5D-5 L and ESAS-r). VTE, bleeding events, and serious adverse events will be collected in real time. Adverse events, in particular the secondary outcomes of recurrent VTE or hemorrhagic events, will be monitored by the Independent Data Monitoring Committee. In the event of excessive bleeding or thrombotic events, this committee will advise on early closure of the trial if necessary. Research staff at recruiting sites will be expected to complete trial case report forms (CRFs) that record evidence of primary and secondary outcome measures. Patients will also be asked for optional consent to have their NHS number collected and to be registered with NHS Information Centre Flagging so that the date and cause of death can be collected without longer term follow up.

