### Outcome measures

The primary outcome measures are: the number of eligible patients identified over 12 months, the number of recruited patients (randomized participants) over 12 months (target recruitment rate of 30% of eligible patients), and the proportion of participants with recurrent VTEs during trial follow up. VTE will be objectively confirmed through radiological investigation. DVT will be confirmed through Doppler ultrasonography or venography. PE shall be confirmed through a computerized tomography (CT) pulmonary angiogram. The secondary outcome measures are: completion of trial protocol, quality of life, symptom assessment, patients’ and relatives’ experiences of taking part in the trial, and the attitudes of clinicians towards the ALICAT trial.

Completion of trial protocol will be assessed six months after randomization to ascertain the attrition rate due to patient choice or death during the study period. Participants choosing to withdraw from either arm of the study protocol will be invited to participate in a qualitative interview to explore their reasons for withdrawal.

Quality of life will be measured using the EORTC QLQ-C30 Version 3.0 and EQ-5D-5 L at three monthly intervals for six months. The EORTC QLQ-C30 [39], Version 3.0, has become a benchmark measure of quality of life in patients with cancer. It contains five functional scales (physical, role, cognitive, emotional and social), three symptom scales (pain, nausea and/or vomiting, and fatigue), global health and quality of life scales, and several other single items. The EQ-5D-5 L [40] is a short quality of life tool, designed to complement other measures and is recommended by the National Institute for Health and Care Excellence for use in economic analyses [41]. The ALICAT study will identify key cost drivers to inform the design of a future definitive phase three trial, which will include a cost utility study. Orders of magnitude of differences in costs and outcomes identified in the EQ-5D-5 L will help in the estimation of anticipated effect sizes for the full trial.

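### Crude percentages of all randomized patients count those lost before six months as free of VTE and bleeding, which modestly understates both risks

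*Protocol article*

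**What the plan says.** The Statistical analysis section names the estimator: "We will also calculate the percentage of patients experiencing recurrent VTE recurrence and bleeding events in both groups with 95% confidence intervals". It also fixes the denominator by intention to treat: "all patients randomized will be included". The section mentions no censoring, person-time or competing event.

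The VTE figure carries weight. Outcome measures lists among the primary outcomes "the proportion of participants with recurrent VTEs during trial follow up". The sample size section says the study will estimate the "proportion of patients who experience recurrent VTEs during follow up, which will inform the design of the phase three RCT". The same section bases its precision on complete arms: "Thirty patients per arm will provide enough power to create a 95% confidence interval around the risk of VTE recurrence".

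Two further statements bear on the point. RCT data collection says: "VTE, bleeding events, and serious adverse events will be collected in real time". The Background describes a single-arm dalteparin study in a similar population, "of whom 185 (55.4%) completed six months of therapy and 109 (33%) completed twelve months".

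**The concern.** A percentage of all randomized patients is the six-month risk only if each patient's status is known to six months, to the event or to death. A patient who leaves observation in week 3 without a recorded VTE stays in the denominator for the full period but can add nothing to the numerator. The plan as written offers no other way to treat that patient, so the percentage is pulled down by an amount that depends on how many are lost and when.

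The VTE proportion is to feed the phase three design, which needs the event risk, the death rate and the loss rate as separate inputs. A crude percentage blends the first and the third. The trial is also open-label: one arm goes on injecting and the other stops. Unequal withdrawal is therefore possible, and it could create or hide a difference in crude percentages when the underlying VTE hazard is the same.

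**Working it through.** **The plan's own figure.** For 30 patients and an observed risk of 50%, the article gives an interval of about 33% to 67%. The Wilson score interval is 33.2% to 66.8%, so the figure reproduces. For a risk of 8% the article gives 0 to 19%; a Wald interval with continuity correction gives 0 to 19.4%. Both take all 30 outcomes as known.

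**Inputs.** The 8% risk is the article's own example, and follow-up is about six months. The article states no loss rate, so 10% and 20% are assumed. As an upper bound I use the cited study: 109/185 = 58.9% completed months seven to twelve, so 41.1% did not.

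**Model.** Constant monthly hazards: λ for VTE, δ for death, μ for loss.
- Crude percentage = λ/(λ+δ+μ) × (1 − exp(−6(λ+δ+μ))).
- Cumulative incidence with death competing and loss censored (the Aalen-Johansen target) = λ/(λ+δ) × (1 − exp(−6(λ+δ))).

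For 8%, λ = −ln(0.92)/6 = 0.01390.

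**Loss only (δ = 0), true risk 8%.**
- 10% loss: μ = −ln(0.90)/6 = 0.01756. Crude = 0.01390/0.03146 × (1 − 0.92×0.90) = 0.4418 × 0.172 = 7.6%, or 5% too low in relative terms.
- 20% loss: μ = 0.03719. Crude = 0.01390/0.05109 × (1 − 0.92×0.80) = 0.2720 × 0.264 = 7.2%, or 10% too low.
- 41% loss: μ = 0.08794. Crude = 0.01390/0.10184 × (1 − 0.92×0.59) = 0.1365 × 0.457 = 6.2%, or 22% too low.

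At 4.1%, the VTE figure quoted for the cited study's extended period, the same three losses give 3.9%, 3.7% and 3.2%, with the same relative shortfalls. Bleeding follows the same arithmetic.

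**Death only (μ = 0).** The two formulas coincide. With 41% dying and none lost, both give 6.2%.

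**Splitting 41% between death and loss**, with the hazard shared in proportion:

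| Died | Lost | Crude | Cumulative incidence | Crude too low by (relative) | Gap in 30 patients |
|---|---|---|---|---|---|
| 41% | 0% | 6.2% | 6.2% | 0% | 0 events |
| 30% | 11% | 6.2% | 6.7% | 6% | 0.1 |
| 20% | 21% | 6.2% | 7.1% | 12% | 0.2 |
| 0% | 41% | 6.2% | 8.0% | 22% | 0.5 |

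At an assumed 20% risk the crude figure is 15.7% against 15.7%, 16.7%, 17.7% and 20.0%, a gap of 0 to 1.3 events in 30.

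**Between arms, same VTE hazard (8%), no deaths.** Equal loss of 20% gives 7.2% in both arms. Loss of 10% against 30% gives 7.6% against 0.01390/0.07334 × (1 − 0.92×0.70) = 6.7%, a spurious gap of about 0.9 points. With 20% also dying in each arm, the crude figures are 6.7% and 5.8%, while the cumulative incidences are 7.1% and 7.0%.

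**Effect on phase three (illustration).** Assume risks of 20% and 10% without attrition, then 20% death and 21% loss, with two-sided 5% significance and 90% power. Crude inputs of 15.7% and 7.8% give 349 per arm; cumulative-incidence inputs of 17.7% and 8.8% give 305. The crude inputs lead to a larger trial here, not an underpowered one.

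**The case against.** The case against rests on five arguments.

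- **The 41% is not lost outcome data.** It is non-completion of therapy in another study, with deaths not separated, and the same section reports 96% trial adherence. In this trial a patient who stops LMWH stays in the intention-to-treat analysis, and events are collected in real time, so stopping treatment need not end observation. This stands. A reader might infer that the risk will be about 22% too low; the documents do not support that.
- **Death is not a source of bias here.** A reader might infer that high mortality makes the percentage too low. As a six-month cumulative incidence it does not, and deaths by arm are already to be reported. This stands.
- **The arms are not shown to be non-comparable.** Nothing in the article says that loss will differ by arm, and equal loss with equal hazards gives equal percentages. This stands; only the conditional form survives.
- **The effect is small.** At 8% risk it is at most 0.5 events in 30, against a planned interval up to 34 points wide. This is true of the size. The shortfall is nevertheless systematic, and the interval carries no allowance for it.
- **Handling of withdrawal belongs in an analysis plan that is not shown.** This stands only in part. The protocol does not leave the estimator open: it names the percentage and its denominator, so the stated analysis itself would have to change.

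On whether loss of 10% to 20% is plausible, the qualitative component seeks 10 to 15 interviews per group, and one group is patients who withdraw. Against about 60 randomized, that is 17% to 25%. This is an interview target and not a forecast, and withdrawal from an arm need not mean loss of outcome data.

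**Conclusion.** The point holds in a limited form. As planned, patients lost before six months without a recorded event count as event-free, and both the VTE and the bleeding percentages are biased downward by non-death loss. The size is about 5% to 10% relative at an assumed 10% to 20% loss, and 22% only if 41% were lost to observation. If outcome follow-up is complete to six months or death, the bias is zero. Comparability between arms is in doubt only if loss differs by arm, which the open-label design makes possible and the article does not predict.

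These figures assume constant hazards and loss unrelated to VTE risk. They do not show that the feasibility conclusion would change. The case for acting is that a primary outcome meant to inform phase three can be estimated better from data already being collected. It is a cheap improvement.

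**What to change.** In the analysis plan, make the main estimate of recurrent VTE, and separately of bleeding, the six-month cumulative incidence in each arm with a 95% confidence interval, by the Aalen-Johansen method. Treat death without the event as competing. Censor at the date outcome follow-up is lost, not at the date LMWH is stopped, so that the analysis remains by intention to treat. Keep the crude percentage of all randomized patients beside it, and report for each arm the number lost to outcome follow-up and the number dead without VTE.

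The cost is a few sentences and a little more analysis. Event dates should follow from the real-time collection; the date of last known outcome status must also be recorded for each patient. The downsides are slightly wider intervals and an assumption that loss is non-informative, which 30 patients per arm cannot test. Showing the crude percentage and the losses alongside lets a reader judge how much that assumption matters.

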### Embedded qualitative study

To explore clinicians’ attitudes towards the trial and patients’ and their relatives’ experiences of participating in the trial, an embedded qualitative study will be undertaken as part of the larger study. The embedded qualitative study will include focus groups with clinicians and semi-structured interviews with patients and their relatives.

#### Clinician focus groups

Focus groups will be conducted with clinicians from oncology, hematology and primary care settings. Six to ten clinicians will be recruited per group, to enable a variety of perspectives while also ensuring that participants have the opportunity to take part in a dynamic discussion [29]. Two focus groups per clinical setting will be undertaken in order to promote trustworthiness of the findings [29]. Where feasible, for the ease of participants and to not limit the sample to clinicians working in one geographical area [30], focus groups will be held at national meetings and educational events. This has previously been undertaken successfully with clinicians who would otherwise be challenging to recruit to individual interviews of focus groups in other settings [31]. A volunteer sample of clinicians from each clinical setting will be recruited to the focus groups, through advertising the group in the conference literature and via social networking, with clinicians encouraged to contact the researchers or attend on the day.

The focus group will be facilitated by two experienced researchers, with one researcher taking the lead and the other documenting non-verbal communication and ensuring that all participants have the opportunity to participate. It can be challenging to encourage participants to discuss issues relevant to them while ensuring that the research objectives are addressed [29] and therefore a topic guide will be developed that addresses: participants’ attitudes to recruiting to the study in terms of recruitment, equipoise, acceptability of intervention and outcome measures; and participants’ experiences of and attitudes to prescribing LMWH, including whether they would extend treatment past six months. However, the researchers will also encourage participants to explore issues pertinent to them.

#### Semi-structured interviews

This component of the study will explore patients’ and their relatives’ attitudes towards participating in the RCT, potential barriers to and concerns about participation, and factors influencing adherence with self-injection (where appropriate). The most appropriate method for exploring these issues is semi-structured interviews [32], which will be undertaken with: patients who decline randomization, trial participants in the intervention arm, trial participants in the control arm, relatives/carers or trial participants (such as a partner, relative or friend), and participants who withdraw from the intervention or control arm.

In total, 50 to 75 participants will be recruited, including 10 to 15 per group. While this is arguably a large sample size for a qualitative study, it is important to ensure that sufficient numbers of patients are included from each group to promote a variety of perspectives and experiences within the sample. A convenience sample of participants will be recruited from the RCT, a common sampling strategy for embedded qualitative studies within trials [33]. All eligible patients taking part in the RCT will be approached until sufficient numbers have been recruited to represent all groups. Initially, participants will be approached by research practitioners at the recruiting site. When signing the consent form for the RCT component of the study, patients will be able to indicate if they consent to being contacted by the qualitative researcher to discuss being interviewed. The research practitioner will then provide the qualitative researcher with the contact details of consenting participants. The qualitative researcher will contact participants to discuss the interview study, and if the patient agrees, arrange a convenient time and location for interview. LMWH is a home-based treatment and a proportion of relatives assume a caring role in administering the medication. Relatives and/or carers will therefore be recruited by patients taking part in the RCT, enabling patients to have control about who they include [34].

It is anticipated that the interview will take place in the person’s home, for their convenience and for the researcher to be able to speak to the person in their natural environment [35], but can be undertaken in a quiet clinic location if preferred by the participant. The qualitative researcher will take written informed consent immediately prior to the interview where appropriate. Interviews will usually be between 30 and 60 minutes in length, but will be terminated earlier if the participant becomes unwell. Patients who do not consent to participate in the RCT component of the ALICAT study will be interviewed as soon as possible after they have been approached to participate in the trial. ALICAT RCT participants and their relatives/carers will be interviewed after they have completed the treatment phase of the trial, approximately 3 to 12 weeks after the 26 week treatment date. Participants withdrawing from the intervention or control arm of the RCT component of the study will be offered the opportunity to be interviewed at the point of withdrawal.

As with the focus groups, the qualitative interviews will follow a topic guide but also allow participants the flexibility to discuss issues important to them [36]. Patients who take part in the intervention or control arms of the trial will be interviewed to explore: their reasons for, and experiences of, participating in the trial; their views and attitudes towards equipoise; and in the case of the intervention participants, the acceptability of LMWH. Patients who decline randomization will be interviewed to explore their understanding of trial processes, their experiences of the first five months of LMWH off-trial and reasons for non-consent. Participants withdrawing from the study will be interviewed to explore the reasons for their withdrawal and to identify potential strategies and support necessary to minimize attrition. Recruitment to trials in patients with advanced cancer is known to be difficult [37] and patient-reported data in the qualitative arm of this study will inform strategies for recruitment in a full phase three RCT. Relatives/carers of patients who take part in the intervention or control arms of the trial will be interviewed to explore their experiences of caring for someone taking part in the ALICAT trial.

